#### Drop out criteria

The operation cannot meet the inclusion criteriaWithdrawing from trial voluntaryPassing away during the trialLosing contacts such as moving residence or changing hospital

### Recruitment

We will recruit eligible participants from 1 July 2020 and complete in June 2021. According to the fixed date of admission of breast cancer patients in two hospitals, we regularly recruit participants at Fudan University Zhongshan Hospital every Monday, and at the other hospital every Thursday. The primary researcher is responsible for the recruitment and can access the medical history of patients after getting permission. Pictures, relevant materials, and informed consent will be used to introduce the program and purpose of the trial, telling patients the advantages and disadvantages of the intervention. We reconfirm and determine the participant of her eligibility according to the inclusion/exclusion criteria. Eligible participants who would have signed the informed consent will finally enter the study.

### Randomization and blinding

Random number sequences are generated in the randomization software by an independent researcher; the 200,000 was used as the seed number to generate 70 random numbers. For avoiding tampering or transillumination, information of trial was written on the two layers of carbonless copy paper, which was placed in sealed, opaque, sequentially numbered envelopes. An independent research assistant will conduct the group allocation. Participants are required to write their name and admission number on the first layer of paper after disclosing the envelopes, random number sequence and group allocation can be seen only on the second layer of paper, and once the two layers of paper are separated, it cannot be restored. After participants sign the informed consent, the rater completes the baseline assessment, then the research assistant who is blinded to the study will perform the group allocation. Eligible participants will be randomly divided into either the MT group or the control group in a ratio of 1:1. After disclosing the envelope, the participant who obtains a paper marked with the number “1” will be allocated to the MT group, while the participant who obtains a paper marked with “2” will be grouped to the control group. Because of the nature of the intervention, rehabilitation therapists and nurses are not blinded, but they are not informed of the trial purpose; the rater, research assistant, and statistician are blinded, and they are also asked not to seek the group allocation and intervention from participants.

### Intervention

Participants are randomly grouped into either the MT group or the control group. Both groups participate in free range-of-motion upper limb exercise from the first day after the operation. Free range-of-motion upper limb exercise is the recommendation of the guidelines and specifications for breast cancer diagnosis and treatment developed by the Chinese Anti-Cancer Association, Committee of Breast Cancer Society (2019 edition) [14]. The control group engages in free range-of-motion upper limb exercise in the usual way, while the MT group receives free range-of-motion upper limb exercise based on MT. The intervention instructions will be provided to participants at the time from the admission to the operation, ensuring they are familiar with their exercise. Both groups are supervised and instructed by nurses and rehabilitation therapists. Upon discharge, each participant will be given an exercise log, which is used to record exercise time and frequency, as well as adverse events. Participants are required to bring the exercise log at every assessment for review. In addition, verbal instruction, a written booklet, and videos designed for the intervention will be provided to the participants for facilitating the intervention at home. What is more, participants in the MT group will be provided with a plane mirror. After discharge, participants are asked to exercise at home and will be supervised by intervention staff every Tuesday or Thursday by WeChat or telephone. For participants with poor adherence, the intervention staff will give them verbal encouragement and motivation and regularly reward participants who adhere to the exercise (e.g., small juicer, vacuum cup, towel, toothpaste). The intervention staff will share health knowledge to both groups biweekly involving diet, self-care, exercise, and sexual life for maintaining the long-term trust of participants in the study. Both groups are asked not to involve in exercises such as arm stretch, yoga, and pilates, but participants who report morning stiffness on their shoulder more than 30 mins are permitted. The elastic bandage is also not allowed in intervention. The intervention in both groups is as follows.

#### Control group

Participants of the control group receive free range-of-motion upper limb exercise from the first day after the operation as shown in Table 1.

**Table 1 Tab1:** BC Rehabilitation program

**• Preparation phase** 1. If possible, exercise in a quiet room. 2. Do not exercise when you feel dizzy, nauseous, or have lower back pain. 3. If you take blood pressure medication, exercise after 30 minutes. 4. If your shoulder appears morning stiffness more than 30 minutes please perform 5-10 minutes arm stretch training combined with massage before exercise. **• BC Rehabilitation** 1. **1–2 days after surgery** a. Please stand relaxed and hold a bouncy ball in the palm of your hand, put your arm in a position with flexed elbows and slightly extended shoulders, then squeeze the ball as hard as possible for 2-3 seconds, then spread and relax fingers. b. Arms are positioned in the same as above, then rotate the wrist clockwise and anticlockwise. Frequency: 10 repetitions a set, 2 sets a group, 2 groups daily. Efficacy: to promote muscle contraction, blood, and lymph flow, and avoid upper limbs swelling 2. **3-7days after surgery.** a. Please stand relaxed, put your arm by your sides, then touch the ipsilateral and contralateral shoulder alternately by your hand of the affected limb. b. keep the exercise in stage 1. Frequency: 10 repetitions a set, 2 sets a group, 2 groups daily. Efficacy: to recover rotation and adduction. 3. **8-14days after surgery.** a. Please stand, put your arm by your sides, raise the arms forward in a range around 120°, perform backward in a range around 60°. b. Please stand, put your arm in a position with flexed elbows and slightly extended shoulders( neutral ), then perform abduction and adduction of the shoulder(shoulder in adduction). c. Please stand, put your arm by your sides, then perform abduction and adduction of the shoulder in a range around 120° d. ** Turn your shoulders forward and backward e. ** please stand in front of the wall, place your palm of the affected arm on the wall and run up by moving your finger until you feel can’t run up more, maintain for 1mins, then run down. Frequency:10 repeats a set, 3 sets a group, 2 groups daily. Efficacy: to promote shoulder flexion, abduction, and adduction. 4. **2-8weeks after surgery** a. Please stand relaxed, put your arms by your sides, then raise your arms forward and backward to an active range of motion as most tolerated b. Please stand relaxed, place your arms in abduction at shoulder height and flex elbows in 90 degrees( 90° of abducted position), then rotate the forearms up and down. c. Please stand relaxed, put your arm by your sides, then perform abduction and adduction of the shoulders to an active range of motion as most tolerated d. Keep the “d and e” in stage 3. Frequency:10 repeats a set, 3 sets a group, 2 groups daily, 4days per week. Efficacy: to stretch and release the softness in the anterior chest wall to avoid the chest wall tightness. **•Attention!** 1. Please don’t forget the “Preparation phase” before your exercise. 2. It’s better not to arbitrarily change the prearranged sequence of exercise for safety and efficacy. 3. At stages 3 and 4, increase the range of motion as tolerated. 4. A muscular glide in the wrist can be seen when you squeeze the ball. 5. Don't bend the elbow when you perform flexion and abduction of the Shoulder. 6. If the pain after exercise persists, please contact the intervention nurse as soon as possible.	

**The movement will be performed without MT for mirror therapy

#### Mirror group

Participants in the MT group receive free range-of-motion upper limb exercise based on MT from the first day after the operation, the program of free range-of-motion upper limb exercise is the same as the control group. The standing mirror that is designed for this trial consists of a plane mirror, an adjustable bracket, and two wheels; the size of the mirror is 70 cm × 50 cm, and the height of the adjustable bracket is 1.2–2 m (Fig. 2). The MT intervention process is as follows:
Preparation: MT will be carried out in a separate, quiet room. Participants are required to remove any accessories (including watches, bracelets, rings, hair bands) on both upper limbs before intervention. Participants choose to sit or stand depending on themselves. Along the midsagittal plane, the standing mirror is placed in front of the participants, the reflective side faces the unaffected limb, and the affected limb is hidden behind the mirror. Participants are asked to lean forward slightly to watch the complete reflection of the unaffected limb in the mirror.Warm-up: Participants will be told to relax and concentrate on the reflection in the mirror and imagine it as the limb on the affected side, and then optionally move the upper limbs for 2~3 min. This process will repeat 3 times.Exercise: The therapist instructs the participants to perform free range-of-motion upper limb exercise as described in Table 1. Participants are asked to watch the reflection in the mirror of their unaffected limb and think of it as their affected upper limb. During the exercise, participants need to concentrate on the reflection in the mirror.

**Fig. 2 Fig2:**
[figure not shown]
The standing mirror

### Potential advert events and exercise adherence

The nurse needs to regularly record the volume of fluid drainage, as well as observe the wound and measure arm circumference. Adverse events include but are not limited to wound drainage volume increases over 50 ml 1 week later after the operation, delayed wound healing, seroma, skin flap necrosis, and persistent shoulder pain. Any adverse event occurring after the entry into this study of participants will be truthfully recorded. The participant who reports adverse events will have the right to withdraw and get free treatment, as well as evaluation. If participants wish to continue the intervention, we still provided exercise to them. Adherence to exercise is deemed to be an attendance of 85% of planned exercise sessions, which is a total of 261 sets. Adherence will be calculated according to the records of the exercise log.

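### The adherence threshold of 261 sets does not follow from the exercise schedule in Table 1, and the rule changes unit from sessions to sets

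*Protocol article*

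**What the plan says.** The section *Potential advert events and exercise adherence* sets the rule: "Adherence to exercise is deemed to be an attendance of 85% of planned exercise sessions, which is a total of 261 sets". It adds: "Adherence will be calculated according to the records of the exercise log". It does not show how 261 was obtained or what counts as a session.

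The schedule is in Table 1, under *Control group*:

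- Stages 1 and 2 (days 1–2 and 3–7): "10 repetitions a set, 2 sets a group, 2 groups daily".
- Stage 3 (days 8–14): "10 repeats a set, 3 sets a group, 2 groups daily. Efficacy: to promote shoulder flexion".
- Stage 4 (weeks 2–8): "3 sets a group, 2 groups daily, 4days per week".

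Movements d and e are listed in stage 3 and kept in stage 4. They are starred, and the table footnote reads "The movement will be performed without MT for mirror therapy". They remain part of the programme: for the mirror arm, *Mirror group* states that "the program of free range-of-motion upper limb exercise is the same as the control group".

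On the source of the data, *Intervention* says "Upon discharge, each participant will be given an exercise log".

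**The concern.** The rule is a proportion of sessions, but its number is in sets, and the two are joined as if equivalent. Table 1 is detailed enough to compute the planned dose under any reasonable unit, and 261 does not fit it.

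What is at stake is the reported adherence and fidelity result. Most of the intervention is exercise at home, and *Trial monitoring and quality control* lists the exercise logs among the items reviewed. If each movement is logged in both daily groups, a threshold of 261 would class a woman as meeting 85% when she had done less than half of the planned mirror-movement sets. If sets are logged once per routine, no participant could reach it. A null result could then be read as occurring despite good adherence, or adherence could appear to be nil, because of the threshold alone.

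**Working it through.** **Inputs, all from Table 1.**

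| Stage | Days | Sets per group | Groups per day | Lettered mirror movements | All listed exercises |
|---|---|---|---|---|---|
| 1 (days 1–2) | 2 | 2 | 2 | 2 | 2 |
| 2 (days 3–7) | 5 | 2 | 2 | 2 | 3 |
| 3 (days 8–14) | 7 | 3 | 2 | 3 | 5 |
| 4 (weeks 2–8) | 6 × 4 = 24 | 3 | 2 | 3 | 5 |

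Stage 2 has two lettered items. The second repeats stage 1, which contains two exercises, so it is two items or three exercises. The mirror count leaves out d and e.

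**Step 1. Reproduce 261.** Planned sets = sum over stages of days × movements × sets per group × groups per day; cut-off = 0.85 × planned sets.

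With mirror movements only and one group a day:

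2×2×2 + 5×2×2 + 7×3×3 + 24×3×3 = 8 + 20 + 63 + 216 = 307; 0.85 × 307 = 260.95, which rounds to 261.

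This match is sensitive to its choices:

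- Stage 4 of 7 weeks (28 days): 8 + 20 + 63 + 252 = 343; 85% = 291.55.
- Stage 2 as three exercises: 8 + 30 + 63 + 216 = 317; 85% = 269.45.

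A wider enumeration of movement counts, units and stage 4 lengths gave other numerical hits, for example 4 + 20 + 21 + 216 = 261 as a full total. Those need movement counts that are inconsistent between stages, or a stage 4 length that Table 1 does not give.

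**Step 2. Use the printed two groups a day.**

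| Unit | Planned total | 85% | 261 as share of plan |
|---|---|---|---|
| Session (one daily group) | 2×14 + 2×24 = 76 | 64.6 | different unit |
| Set, once per whole routine | 8 + 20 + 42 + 144 = 214 | 181.9 | 122.0% |
| Set, per mirror movement | 16 + 40 + 126 + 432 = 614 | 521.9 | 42.5% |
| Set, per listed exercise (stage 2 as three) | 16 + 60 + 210 + 720 = 1006 | 855.1 | 25.9% |
| Set, per lettered item (stage 2 as two) | 16 + 40 + 210 + 720 = 986 | 838.1 | 26.5% |

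Neither the totals nor the cut-offs include 261.

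**Step 3. Restore one omitted factor at a time.**

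- Two groups a day, still without d and e: 614 to 634 planned; cut-off 521.9 to 538.9.
- One group a day, with d and e: 493 to 503 planned; cut-off 419.05 to 427.55.

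Both omissions are needed to arrive at 261.

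**Step 4. Denominator if only the log is used.** The log starts at discharge and length of stay is not given. Assuming discharge after day 3, 7 or 14, the sessions left are 22 + 48 = 70, 14 + 48 = 62 or 48. The 85% values are 59.5, 52.7 and 40.8, so the cut-offs are 60, 53 and 41.

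**The case against.** The strongest reply is that the explanation is fitted backwards. The article shows no derivation, and reaching 307 takes several choices, including counting stage 2 item b as one movement. That is fair: 307 is the best candidate for the origin of 261, not a demonstrated one. The mismatch with Table 1 does not depend on it.

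Movements d and e may have been left out on purpose, since they are done without the mirror, and a count limited to mirror movements is a legitimate fidelity measure. The text does not say so, and the programme is shared by both arms. If it is granted, two groups a day still doubles the cut-off to 522. The error may then lie in Table 1 rather than in the threshold, and that possibility stands.

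The sentence can also be read with 261 as the whole plan rather than the cut-off. None of the planned totals (76, 214, 614, 986, 1006) is 261, so the mismatch remains.

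The consequences depend on how the log counts, and neither the log nor the full protocol is shown. This also stands: the percentages are a range over units, not one error rate. The unit being left to another document would be no fault in itself. The fault is that the article prints a number that conflicts with its own table.

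Finally, adherence is not a listed outcome or a model covariate, and the article does not say that it defines the modified intention-to-treat set. This limits the severity.

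**Conclusion.** The point holds as a minor error. The threshold of 261 sets does not follow from Table 1 as printed, and the sentence changes unit without saying how sessions convert to sets. It is probably the 85% cut-off of a 307-set count that omits the second daily group and movements d and e.

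Against the printed schedule, 261 is 42.5% of the mirror-movement sets, about 26% of all listed-exercise sets, or more than the whole plan if sets are counted per routine. These figures treat 261 as the cut-off and assume a six-week stage 4 at four days a week.

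The effect is confined to who is classed as adherent. *Data analysis* names radiotherapy, dominant hand and type of surgery as covariates and describes no analysis by adherence, so the GEE comparison of the arms does not change.

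**What to change.** Confirm the number of groups per day and the six-week stage 4. Then choose one unit and state both the planned total and the cut-off.

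- **Preferred:** keep the sentence's own unit and define a session as one daily group. Adherence is then at least 65 of 76 sessions: two a day for 14 days, then two a day on 4 days a week for 6 weeks. This applies equally to both arms.
- **If sets are kept:** state 182 of 214 routine sets, or 522 of 614 sets of the movements other than d and e, and say that d and e are not counted.
- **If 261 of 307 was intended:** correct the two groups a day in Table 1 and state that only the mirror movements, done once a day, are counted.

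Because the log begins at discharge, also say either that in-hospital sessions come from staff records or that the denominator starts at discharge.

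The cost is one corrected sentence or one correction to Table 1. A denominator from day 1 also needs a staff record of in-hospital sessions; a denominator from discharge needs only the discharge date. Make the change before adherence is calculated.

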### Outcomes measures

Outcomes will be measured by a trained rater who is blinded to the group allocation at baseline (T0) and at 2 weeks (T1), 4 weeks (T2), and 8 weeks (T3) after the operation. It is necessary to mention that the four time points are not originally registered time points; the reason for the adjustment is as follows. Firstly, the investigation and preliminary experiment were conducted after the originally registered protocol, it was found that the four time points in this protocol are significant points in observing shoulder rehabilitation, compared with originally registered time points, and using these four time points can achieve the aim of measuring shoulder function without increasing workload. Secondly, patients regularly follow up at these time points, which will facilitate the rater of conducting measurement face to face with participants on time. The investigation and preliminary experiment are not within this study, and the change occurred before the study began. Participants’ demographic information and medical history are collected at baseline, and the primary and secondary outcomes are as follows.

#### Primary outcome

To explore the effects of MT on shoulder function, shoulder joint ROM on the affected limb is the primary outcome. An arm goniometer will be used to obtain shoulder ROM measurement including forward flexion, internal rotation, external rotation, and abduction. We follow Struyf and Meeus’ recommendations to conduct the goniometric shoulder joint ROM measurements [28]. Participants sit and put their arms by their sides. Before the assessment, they will be asked to move their shoulders and stretch their arms to relax the muscle, then move the affected arm following the instructions as possible as they can until they feel tired. Active external rotation and internal rotation are measured in 90° of the horizontal abducted position of the shoulder; meanwhile, the rater will press the participants’ acromion of the scapula to avoid a joint compensatory.

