#### Sample size

The primary outcome in this study is shoulder ROM, which is the main effect indicator for sample size estimating in this randomized controlled trial. Referring to Cohen’s effect size value of 1.3799 in the study of Başkaya et al. [25], to achieve 95% power and 0.05 error range, 30 of the total sample size were calculated using the G-power 3.1 software. However, a larger sample size was planned to be used in this trial due to repeated measurement. We used the GLIMMPSE software for repeated measurement calculation with the shoulder flexion range of motion as the main effect indicator that refers to the results of Başkaya et al. [25]. We choose a test power of 0.95 and a type 1 error rate of 0.05, 58 of sample size was calculated, considering 20% dropout rate, the actual total sample size is 70.

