### Data analysis

Data analysis will be processed by an independent statistician and primary researcher using the SPSS24.0 software. All statistical tests will be double sides; the statistical significance is set at *p* value < .05. Means and standard deviation or median and inter-quartile ranges will be calculated for continuous variables normally distributed and non-normally distributed, respectively. Categorical variables will be described as frequencies (*f*) and percentages (%). Demographics and other baseline values will be analyzed using the independent two-tailed *t*-test, non-parametric Mann-Whitney *U*-test, and chi-square test.

This study will adopt the modified intention-to-treat (mITT) principle. The effects of the intervention on primary and secondary outcomes (excluded arm circumference and incidence of lymphedema) between the groups will be analyzed by generalized estimating equation (GEE) from treatment, time points, and the interaction between group and time. Observed values of those outcomes at four assessments time points will be put into GEE, selecting the auto-correlation matrix and the robust standard error estimation method. Taking outcome index as the response variable, the group, time, and interaction of group and time will be incorporated into the model, in addition, selecting radiotherapy, the dominant hand, and type of surgery as covariates. The model includes the main effect and interaction effect, paired comparison variables will be selected, and the least significant difference (LSD) method will be used to adjust the multiple comparison effect. Arm circumference and incidence of lymphedema will be analyzed at each measurement time point between groups using the independent two-tailed *t*-test and chi-square test. In case of missing data, if missing data is completely random, the sample will not be included in the final data analysis. If missing data is incomplete random missing or non-random missing, multiple interpolations will be used to complete missing values.

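### The primary outcome is four shoulder movements with no decisive movement, model term or visit, so the stated 0.05 does not hold for the primary claim; the sample size rests on flexion alone

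*Protocol article*

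**What the plan says.** Under Primary outcome, the protocol states that "shoulder joint ROM on the affected limb is the primary outcome" and then lists what is measured: "An arm goniometer will be used to obtain shoulder ROM measurement including forward flexion, internal rotation, external rotation, and abduction". It defines no composite of the four angles and gives none of them the lead.

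Under Outcomes measures, assessments take place "at baseline (T0) and at 2 weeks (T1), 4 weeks (T2), and 8 weeks (T3) after the operation". No post-operative visit is called primary.

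Under Data analysis, "All statistical tests will be double sides", with significance set at p < .05. On the model, "Observed values of those outcomes at four assessments time points will be put into GEE", with group, time and their interaction as terms. Paired comparisons follow, and LSD is described as the adjustment for multiple comparisons. No rule covers the four movements jointly.

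Under Sample size, the repeated-measures calculation was done "with the shoulder flexion range of motion as the main effect indicator", with power 0.95 and a type 1 error rate of 0.05. It gave 58 women, raised to 70 for 20% dropout.

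**The concern.** The sample size is built for one movement, but the declared primary outcome is four. Nothing in the analysis section brings the four back to one: there is no composite, no lead movement, no decisive model term and no rule across movements. The one multiplicity method named, LSD, leaves each comparison at its own 0.05.

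A difference in a single movement, perhaps at a single visit, could therefore be presented as a positive result on the primary outcome, and the text would not rule it out. The quoted error rate and power describe one flexion analysis. They do not describe the claim that the trial could end up making.

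**Working it through.** **Inputs from the protocol.** Four movements (Primary outcome); three post-operative visits (Outcomes measures); two-sided 0.05 for every test and LSD for paired comparisons (Data analysis); d = 1.3799, power 0.95, total N of 30, then 58, then 70 (Sample size); 1:1 allocation (Randomization and blinding).

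**Step 1: the plan's own figures.** A two-sample t-test (noncentral t, two-sided 0.05, d = 1.3799) has power 0.940 with 14 per arm and 0.954 with 15 per arm. The total of 30 is therefore reproduced. The 70 is reproduced as 58 × 1.2 = 69.6; after 20% dropout it leaves 70 × 0.8 = 56, or 28 per arm. The 58 cannot be checked, because the means, standard deviations, correlations and tested hypothesis behind it are not given. In none of these steps is the 0.05 divided over movements or visits.

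**Step 2: one test per movement (4 tests).** If independent, the chance of at least one false positive is 1 − 0.95^4 = 0.185. The protocol gives no correlations between movements, so a range is assumed (equal correlation r between all pairs of test statistics):

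| Assumed r | At least one false positive in 4 tests |
|---|---|
| 0 | 18.5% |
| 0.3 | 17.4% |
| 0.5 | 15.6% |
| 0.7 | 13.0% |
| 0.8 | 11.4% |

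**Step 3: visit contrasts also count, with no preceding joint test (4 × 3 = 12 tests).** If independent, 1 − 0.95^12 = 0.460. By simulation of correlated normal test statistics, with assumed correlations between movements and between visits:

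| Between movements | Between visits | At least one false positive in 12 tests |
|---|---|---|
| 0.3 | 0.5 | 39% |
| 0.5 | 0.5 | 36% |
| 0.7 | 0.7 | 27% |
| 0.8 | 0.8 | 21% |

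If visit contrasts were read only after a significant joint test for that movement, the risk could not exceed that of the joint tests themselves, which is the range in step 2.

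**Step 4: what correction would cost in power.** Bonferroni over four movements gives 0.05/4 = 0.0125 per test. Holm is never less powerful than this. With 28 per arm, two-sample t-test:

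| Effect | Power at 0.05 | Power at 0.0125 |
|---|---|---|
| d = 1.3799 (stated in the protocol) | 0.999 | 0.994 |
| d = 0.963 (assumed) | 0.943 | 0.842 |

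The value 0.963 is the effect at which a simple t-test with 29 per arm has 95% power. The protocol did not obtain 58 in this way, so this row is only an illustration.

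**The case against.** Four arguments can be made for the plan.

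*The planned model gives one interaction test per movement, and visit contrasts may only be follow-up.* This is a fair reading. A reader might infer that the trial has 12 chances of success and a 46% error rate. The protocol does not support that as a plain statement: it sets no success rule, does not say how the four movements enter the model, and does not say that an isolated visit contrast counts. The 46% also needs independence, which is implausible for angles of one shoulder measured repeatedly. Equally, the protocol does not name the interaction as decisive, and four such tests still exceed 0.05.

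*The trial calls itself exploratory (Objectives).* That softens the point. But the trial also declares a primary outcome and powers it at 95% with a stated type 1 error rate, and those claims need a defined test.

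*A statistical analysis plan may settle it.* Which model term decides could be left to such a plan. Here, however, the protocol itself fixes the undivided 0.05 and presents LSD as the adjustment, so a later plan would have to change this text and not merely complete it.

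*The planned number may carry a correction.* A reader might infer that protecting all four movements would cut power from about 94% to 84%. That rests on the assumed d = 0.963. At the protocol's own 1.3799 the cost is negligible, although that effect is not shown for the other three movements. Their power is not shown, which is different from being shown to be inadequate.

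**Conclusion.** The point stands. As written, the stated 0.05 does not apply to a claim on shoulder ROM, and the stated 0.95 power applies to flexion only. With one test per movement, the false-positive risk is about 11 to 18.5%: two to nearly four times the nominal level. It rises to about 21 to 39% only if unprotected visit contrasts also count as success, with 46% as the figure under independence. The counts of tests come from the protocol. The correlations, and treating each movement as a separate analysis, are assumptions; the second is the natural reading because no composite is defined. The loss of power under a correction cannot be fixed from the document.

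**What to change.** Name forward flexion of the affected arm as the single primary outcome, since it is the basis of the sample size, and state one decisive test. Two choices are reasonable: the between-group contrast at 8 weeks, when the intervention ends, or the joint group-by-time test over the visits. The Sample size section names no visit, so 8 weeks would be a choice and not something already implied. Make the other three movements and the remaining visit contrasts secondary, and replace LSD with Holm or fixed-order testing.

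Alternatively, keep all four movements primary, with one decisive test each and Holm across the four.

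The choice must be made and recorded before any comparative look at the data. The section Trial monitoring and quality control requires an interim analysis at the mid-term examination, so waiting until the database is locked would be too late.

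The cost is an amendment and a registry update, with no new data. Under the first option three movements lose primary status. Under the second some power is lost: almost none at d = 1.3799, and about 10 percentage points (0.943 to 0.842) at the assumed d = 0.963 if a movement has to pass at 0.0125.
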